### Sample size and power calculation

The target sample size is 326 participants in each trial arm. With a sample size of 652 participants in total, at an alpha of 0.05, the study has 85% power to detect a 10% absolute difference in surveillance rates between the intervention and control groups. This assumes a baseline surveillance completion rate of 10% in standard care, derived from a similar RCT in the USA comparing the effect of mailed outreach and PN on HCC surveillance participation.^16^

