### Statistical analysis

Descriptive statistics will be used to summarise baseline patient characteristics, primary and secondary outcomes from the two study groups. Continuous variables will be reported using number of observations, arithmetic mean, SD, median and minimum and maximum values; categorical variables will be summarised by frequencies and percentages. A two-way repeated measures analysis of variance will be performed, with time as a repeated factor, to compare the two intervention arms with respect to the primary outcome. Intention-to-screen analyses will be undertaken. Additionally, cost-effectiveness analysis will be performed using the return on investment (ROI) tool developed by Public Health England. The interactive ROI Tool can help estimate ROI, cost savings and health outcomes from specific public health interventions to guide authorities and policymakers to invest in initiatives that maximise health and economic benefits.^19^

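### The stated 85% power does not follow from the inputs beside it: 326 per arm gives about 95% power for 10% versus 20%, and the input that would lead to 326 is not stated

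*Protocol article*

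**What the plan says.** The section Sample size and power calculation gives a short, apparently complete set of inputs:

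- Size: "The target sample size is 326 participants in each trial arm", that is 652 in total.
- Significance level: "at an alpha of 0.05", with no statement of one or two sides.
- Effect: "to detect a 10% absolute difference in surveillance rates between the intervention and control groups".
- Control rate: "This assumes a baseline surveillance completion rate of 10% in standard care", taken from a similar randomised trial in the USA.
- Result: "the study has 85% power to detect a 10% absolute difference in surveillance rates between the intervention and control groups".

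The Abstract gives 1:1 allocation. The power sentence opens with "With a sample size of 652 participants in total", so the 85% is attached to everyone randomised. The section names no test, loss allowance, alpha adjustment or design effect.

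**The concern.** A 10% baseline and a 10-point absolute difference mean 10% versus 20%. For that contrast 326 per arm is far more than 85% power requires, so at least one of the printed figures is not the one used in the calculation.

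The sample size paragraph justifies enrolling 652 people, here under a waiver of consent, and it will frame how a null result is read. If its figures do not reproduce, a reader cannot tell which control rate, alpha or effective sample size the trial was designed on, and so cannot say what difference the trial can reliably detect.

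**Working it through.** **Inputs.** From Sample size and power calculation: n = 326 per arm, alpha = 0.05, p1 = 0.10, difference 0.10, so p2 = 0.20. From the Abstract: 1:1 allocation. Two-sided testing is assumed because the side is not stated. Critical values: z(0.975) = 1.960, z(0.85) = 1.036.

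**Step 1: attempt to reproduce the 85%.** Two-proportion z-test with pooled variance under the null:

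power = Φ{ [ |p2 − p1| − z(0.975) · √(2p̄(1 − p̄)/n) ] / √[ (p1(1 − p1) + p2(1 − p2))/n ] }, with p̄ = 0.15.

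- √(2 × 0.15 × 0.85/326) = 0.02797
- √((0.09 + 0.16)/326) = 0.02769
- (0.10 − 1.960 × 0.02797)/0.02769 = 0.04518/0.02769 = 1.632
- Φ(1.632) = 0.949

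The stated inputs give 94.9%, not 85%.

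**Step 2: the size that 85% requires.**

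n = [ z(0.975) · √(2p̄(1 − p̄)) + z(0.85) · √(p1(1 − p1) + p2(1 − p2)) ]² / (p2 − p1)²

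= (0.9897 + 0.5182)² / 0.01 = 227.4, so 228 per arm, 456 in total. With continuity correction it is 247 per arm, 494 in total. The planned 652 is 652/456 = 1.43 times the uncorrected requirement.

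**Step 3: does the choice of test explain it?** Power at 326 per arm, and size per arm for 85% power, for 10% versus 20%:

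| Method | Power at 326 | n per arm for 85% |
|---|---|---|
| Pooled z, two-sided | 94.9% | 228 |
| Unpooled z | 95.1% | 225 |
| Arcsine | 95.2% | 223 |
| Continuity-corrected | 93.6% | 247 |
| Fisher exact | 94.0% | about 245 |
| One-sided pooled z | 97.4% | 182 |

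All of these lie about 9 to 12 points above 85%. Halving alpha to 0.025, as one might for the two primary outcomes, still leaves 91.1% (273 per arm for 85%).

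**Step 4: the difference that 326 per arm detects.** Holding the baseline at 10% and power at 85%, the formula in step 1 gives a detectable difference of about 8.1 points, not 10.

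**Step 5: which unstated inputs would lead to 326?** None of these is in the article.

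- *Loss allowance of about 30%.* 228/0.70 = 325.7, rounded up to 326. Starting from the unrounded 227.39 gives 324.8, so 325; the exact match depends on rounding first.
- *A higher control rate with the same 10-point difference.* 19% versus 29% gives 85.0% at 326 per arm; 20% versus 30% gives 84.0% (336 per arm for 85%).
- *Alpha split four ways.* At 0.05/4 = 0.0125, z = 2.498, and (0.10 − 2.498 × 0.02797)/0.02769 = 1.089, so power is 86.2% (317 per arm for 85%).

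Three different designs come within about 1.2 points of the stated power or, for the loss allowance, match the stated size. The numbers alone do not choose between them.

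**The case against.** **This is a condensed article.** The test, its sidedness and any loss allowance are commonly left to the full protocol or analysis plan, and their absence here is no fault. That is right, and it limits the point to one sentence. It does not rescue the sentence, which makes a positive claim about 652 participants at alpha 0.05 with a 10% baseline. An unseen document could explain where 326 came from; it could not make 85% the power for those inputs.

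**The error is on the safe side.** On the stated inputs the trial has more power than it claims. Nothing in the analysis is biased by this and no one needs to be added. This also stands, and it is why the point is a reporting error of moderate weight and not a defect in the design.

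**Tempting stronger reading: a hidden 30% loss that conflicts with the analysis set.** Because 228/0.70 rounds up to 326, a reader might infer an undisclosed allowance for 30% loss, and then a clash with the Statistical analysis section, where "Intention-to-screen analyses will be undertaken". The documents do not support this. No loss is stated, and the match depends on rounding and is not unique (step 5). Even if an allowance existed, it need not contradict that analysis. Data collection provides for recording why participants are removed from the surveillance pathway, so some departures are foreseen, and how they are handled may be set out elsewhere. Nor does the article say that attendance is read from hospital records; it says attendance is entered on the study database. Complete ascertainment would be the reader's own assumption.

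**A second tempting reading: the trial could be cut to 456.** That would follow only if 10% were secure as the control rate. The article assigns the 10% to standard care, while both randomised arms receive the bespoke invitation. The computed surplus should not be taken as a reason to enrol fewer.

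**Conclusion.** The power figure is wrong as written. With 326 per arm, 10% versus 20% and two-sided alpha 0.05, power is 94.9% (93.6% with continuity correction), about 10 points above the stated 85%. For 85%, about 228 per arm suffice (247 with continuity correction). The result assumes a two-sided comparison of two independent proportions with all 652 analysed; a one-sided test widens the gap, and no standard variant tried closes it.

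On the stated inputs the error understates power. The article does not show which assumption produced 326, and no single explanation should be presented as the answer. Severity is moderate: the paragraph cannot be reproduced, but on its own inputs the trial is not short of participants.

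**What to change.** Keep the total at 652 and correct the sample size paragraph in one of two ways, according to what was actually done:

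1. If the printed inputs are the real ones, restate the power as about 95% for 10% versus 20%, and name the test and its sidedness.
2. If another input was used, state it and give the power that follows from it: the loss allowance with its basis and the number expected in the analysis, the alpha split with the outcomes it covers, or the control-arm rate with its source.

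The two should not be mixed. A paragraph that prints 95% for a 10% control rate and also says that a different control rate applies would again fail to reproduce.

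The cost is rewording one paragraph, with a matching correction in the full protocol if it carries the same sentence. Enrolment, arms and procedures do not change.

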### Patient and public involvement

Key stakeholders, including patient advocacy groups (The British Liver Trust, The Hepatitis C Trust and Groundswell) and patient advocates, were consulted and engaged during the design of the protocol. To design the interventions in line with patients’ needs and preferences, we organised five co-production workshops (three face-to-face and two online) comprising patients with lived experience of liver disease and charity representatives. These workshops highlighted motivational factors and barriers to attending HCC surveillance among patients. Patient preferences and advice were sought to guide the development of the mailed letter and explanatory postcard about the surveillance process, including language used, informational content and addition of illustrations, to maximise the effectiveness of the outreach material.^12^

## Ethics and dissemination

Ethical approval to conduct the trial has been obtained from the Aberdeen Research Ethics Committee (Ref: 335338). A waiver of consent has been granted by the ethics board. The waiver of consent was deemed ethical as (i) the study carries minimal risk since all patients will receive HCC surveillance as per standard of care, (ii) the waiver of consent will not adversely affect the rights or welfare of the participants and (iii) necessitating consent would introduce volunteer bias, undermining the generalisability of the study and its validity as a population health study. Data will be stored in a secure environment with password protection, and every effort will be made to maintain confidentiality and anonymisation in line with General Data Protection Regulation. Findings of this trial will be shared internationally through publication in peer-reviewed journals and presentation at medical conferences.
